**Figure 5 Flow chart of Cluster randomized Study Procedures**

## **3.5 Expected Outcome**

The study will provide data on the frequency of BP screening among adolescents living with HIV in the selected facilities. The evidence of the effectiveness of the proposed theory of planned behaviour-based intervention on improving healthcare worker adherence to the guidelines and the physiologic measures of the adolescents will also be provided.

## **3.6 Ethical Consideration**

Ethical approval will be sought from the Ghana Health Service Ethics Review Committee. Permission will be sought from the regional and respective municipal health directorates of the study areas and the managers of the health facilities. Permission will also be obtained from the heads of medical records in the respective facilities before extracting data from the client care booklets.

## **3.6.1 Voluntary Participation**

All potential study participants will be made aware that participation in the study is entirely voluntary and that they are free to drop out of the study (and can choose not to disclose reasons for dropping out) at any time with no negative consequence. All participants will sign a written informed consent before enrolment into the study. The consent form will describe the aim of the study, procedures, risks, benefits and compensation. The investigator will be available to answer all questions and allow time for potential participants to think through them and make a decision. Consent from the caregivers of adolescents below 18 years will be sought, followed by participant ascent before participating in the study.

## **3.6.2 Privacy and Confidentiality**

Electronic data will be stored in a password-protected file and hard data in locked cabinets which will only be accessible to the principal investigator and supervisors. Study codes will be assigned to each participant and used as a form of identification on the questionnaires. Data will only be used for academic or publication purposes. The data will be destroyed after ten years.

## **3.6.3 Risks**

There are no foreseen severe physical risks or side effects to the participants due to participating in the study. Participants will be informed to anticipate some minor discomfort while checking both office and ambulatory blood pressures. Nose masks and hand sanitizers will be provided for the study team and participants to minimize the risk of a COVID-19 infection.

## **3.6.4 Compensation**

Adolescent participants coming for follow up assessments outside their scheduled facility visits will have their transportation reimbursed.

## **3.6.5 Declaration of Conflict Of Interest**

The PI has no conflict of interest to declare.

## **3.7 Funding**

The study will be supported by the University of Ghana and the Yale University Academic Partnership for HIV Comorbidity Research Training in Ghana and funded by Fogarty International Center Grant.

## **3.8 Protocol Amendments**

The Ghana Health Service Ethics Review Committee will be informed of all amendments following changes/additions to the protocol and consent form.

**Table 2** **Study Timelines**

| **Timelines** | **2022** | | | | | | | | | | | | | **2023** | | | | |
| --- | --- | --- | --- | --- | --- | --- | --- | --- | --- | --- | --- | --- | --- | --- | --- | --- | --- | --- |
| **Activity** | J | F | M | A | M | J | J | Au | S | O | N | D | J | | F | M | A |  |
| Protocol development |  |  |  |  |  |  |  |  |  |  |  |  |  | |  |  |  |  |
| Ethical approval and stakeholder engagement |  |  |  |  |  |  |  |  |  |  |  |  |  | |  |  |  |  |
| Orientation for research assistants |  |  |  |  |  |  |  |  |  |  |  |  |  | |  |  |  |  |
| Orientation for facility research coordinators |  |  |  |  |  |  |  |  |  |  |  |  |  | |  |  |  |  |
| Baseline assessment |  |  |  |  |  |  |  |  |  |  |  |  |  | |  |  |  |  |
| Orientation on CPG for screening and management of hypertension among adolescents |  |  |  |  |  |  |  |  |  |  |  |  |  | |  |  |  |  |
| Orientation on hypertension among adolescents living with HIV |  |  |  |  |  |  |  |  |  |  |  |  |  | |  |  |  |  |
| Intervention implementation |  |  |  |  |  |  |  |  |  |  |  |  |  | |  |  |  |  |
| Data collection and analysis |  |  |  |  |  |  |  |  |  |  |  |  |  | |  |  |  |  |
| Report writing, presentation and publication |  |  |  |  |  |  |  |  |  |  |  |  |  | |  |  |  |  |

| **Item** | **Budget lines** | **Unit Cost** | **Quantity** | **Duration (days/Months)** | **Frequency** | **Total** | **Comments** |
| --- | --- | --- | --- | --- | --- | --- | --- |
| Ethical Approval and stakeholder engagements | Cost for protocol review | 500 | 1 | 1 | 1 | 500 |  |
|  | Transport to health facilities | 50 | 12 | 1 | 1 | 600 | 2 facilities to be visited per day |
|  | **Subtotal** |  |  |  |  | **1,100** |  |
| Orientation for Research assistants(5) | Snack and Lunch | 60 | 5 | 2 | 1 | 600 | five research assistants to help with data collection. |
|  | Facilitation | 350 | 2 | 2 | 1 | 1,400 |  |
|  | transport for participants | 50 | 5 | 2 | 1 | 500 |  |
|  | Transport for facilitator | 50 | 2 | 2 | 1 | 200 |  |
|  | **Subtotal** |  |  |  |  | **2,700** |  |
| Orientation for Facility Research coordinators | Snack and Lunch | 60 | 24 | 1 | 1 | 1,440 | Each facility will have one study coordinator |
|  | Facilitation | 350 | 2 | 1 | 1 | 700 |  |
|  | Transport for participants | 50 | 24 | 1 | 1 | 1,200 |  |
|  | Transport for facilitator | 50 | 2 | 1 | 1 | 100 |  |
|  | **Subtotal** |  |  |  |  | **3,440** |  |
| Records review | Programming for Kobokolect | 3000 | 1 | 1 | 1 | 3,000 | Data collection to be done on the kobokolect platform |
|  | Transport for data collectors | 50 | 5 | 5 | 2 | 2,500 | a total of about 480 records to be reviewed. The assumption is for 20 records to be reviewed per day per data collector at baseline and 6months after intervention |
|  | Hiring of tablets | 15 | 5 | 9 | 2 | 1,350 |  |
|  | **Subtotal** |  |  |  |  | **6,850** |  |
| orientation on CPG for screening and management of hypertension among adolescents | TPB based questionnaire and pre/post-test papers | 2 | 96 | 1 | 2 | 384 | 96 HCWs(4 per facility) |
|  | Snack and Lunch | 60 | 98 | 2 | 1 | 11,760 |  |
|  | transport for participants | 50 | 96 | 2 | 1 | 9,600 |  |
|  | Transport for facilitator | 50 | 2 | 2 | 1 | 200 |  |
|  | **Subtotal** |  |  |  |  | **21,944** |  |
| Orientation on hypertension among adolescents living with HIV | Snack and Lunch | 60 | 50 | 1 | 1 | 3,000 |  |
|  | transport for participants | 50 | 48 | 1 | 1 | 2,400 |  |
|  | Transport for facilitator | 50 | 2 | 1 | 1 | 100 |  |
|  | **Subtotal** |  |  |  |  | **5,500** |  |
| Intervention package | Paediatric sphygmomanometers | 200 | 12 | 1 | 1 | 2,400 | 10 intervention and 10 control facilities will be used. Controls will receive the package after the follow-up period |
|  | Guidelines for hypertension management | 20 | 12 | 1 | 1 | 240 |  |
|  | Posters | 5 | 12 | 1 | 1 | 60 |  |
|  | BP reference guide | 15 | 12 | 1 | 1 | 180 |  |
|  | **Subtotal** |  |  |  |  | **2,880** |  |
| Follow up | Ambulatory BP machine | 900 | 12 | 1 | 1 | 10,800 |  |
|  | Weighing Scale | 50 | 5 | 1 | 1 | 250 |  |
|  | Stadiometer | 100 | 5 | 1 | 1 | 500 |  |
|  | T&T for adolescent participants | 20 | 480 | 1 | 2 | 19,200 |  |
|  | **Subtotal** |  |  |  |  | **30,750** |  |
|  | **Grand Total** |  |  |  |  | **75,164** |  |

# **5.0 Appendix**

## **Appendix II: Questions for elicitation study**

Your patient is an adolescent (10-17 years) living with HIV. The target behaviour is measuring the patient’s blood pressure (BP). Please take a few minutes to list your thoughts about the following questions:

**Behavioural beliefs (Attitude)**

1. What do you believe are the advantages of measuring the patient’s blood pressure?
2. What do you believe are the disadvantages of measuring the patient’s blood pressure?
3. Is there anything else you associate with measuring the patient’s blood pressure?

**Normative beliefs (Subjective norms)**

1. Are there any individuals or groups who would approve of your measuring the patient’s BP?
2. Are there any individuals or groups who would disapprove of your measuring the patient’s BP?
3. Is there anything else you associate with measuring the patient’s blood pressure?

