**Exclusion criteria**

- Does not consent to part take in the study

1. **Sample size**

Francis and colleagues recommended that at least 25 participants be included in any elicitation phase of research using an open-ended questionnaire(Francis et al., 2004). With an anticipated 50% response rate as observed in a similar study (2), at least 50 participants will be enrolled in this elicitation study.

1. **Elicitation Of Behavioral, Normative And Control Beliefs**

As recommended in the manual for constructing questionnaires based on the theory of planned behavior(Francis et al., 2004) and adapted for this study, the questions to be used to elicit the health workers’ behavioral, normative, and control beliefs can be found in the appendix.

1. **Analysis**

Two individuals, including the PI, will analyze the content of the responses by developing themes, labelling them and listing them in order of frequency. The most frequently reported beliefs, described as the modal set, will be used to develop the instrument to measure the health workers’ behavioural, normative, and control beliefs. As recommended, at least 75% of all beliefs listed will be included in the tool to cover the belief’ population” adequately.

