**Control beliefs (perceived behavioural control)**

1. What factors or circumstances enable you to measure the blood pressure of adolescents living with HIV?
2. What factors or circumstances make it difficult or impossible for you to measure the blood pressure of adolescents living with HIV?
3. Are there any other issues that come to mind when you think about measuring the blood pressure of an adolescent living with HIV?

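### In the elicitation questions, the third normative-belief question repeats the third attitude question word for word, so the normative section has no open probe about other people's views.

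*Protocol*

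**What the plan says.** Section 3.2.3 of the Protocol plans an elicitation study to collect health workers' behavioural, normative and control beliefs about checking adolescents' blood pressure. The questions are in Appendix II, three under each heading.

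- Behavioural beliefs (Attitude), question 3: "Is there anything else you associate with measuring the patient’s blood pressure".
- Normative beliefs (Subjective norms), question 1: "Are there any individuals or groups who would approve of your measuring the patient’s BP". Question 2 asks the same about disapproval. Question 3 is the attitude question again, in the same words, beginning "Is there anything else you associate with measuring the".
- Control beliefs, question 3: "Are there any other issues that come to mind when you think about measuring the blood pressure of an adolescent living with HIV".

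Under Analysis in section 3.2.3, two people "will analyze the content of the responses by developing themes, labelling them and listing them in order of frequency". The text continues: "The most frequently reported beliefs, described as the modal set, will be used to develop the instrument", and "at least 75% of all beliefs listed will be included in the tool". Section 3.2.4 builds the draft questionnaire from these responses. Section 3.2.6 f then regresses intention on attitudes, subjective norms and perceived behavioural control.

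**The concern.** Each block of questions is there to draw out one construct. In the normative block the first two questions do so by pointing at individuals or groups. The third points only at the act of measuring blood pressure, which the respondent has already been asked about three questions before. The natural answer is to repeat an attitude belief or to leave the space blank.

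At stake is the content of the subjective-norm scale. If the people whose opinion matters, or the form their influence takes, are not brought out at elicitation, the questionnaire has less to build norm items from. A thin or mixed norm scale would make the survey's comparison of the three predictors of intention, which serves objective 1, less reliable.

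**Working it through.** No arithmetic decides this point; it rests on setting the texts side by side.

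**The one figure attached to the elicitation study.** Section 3.2.3 cites a recommendation of "at least 25 participants be included in any elicitation phase of research using an open-ended questionnaire" and expects a 50% response rate. 25 / (1 − 0.50) = 50, which agrees with the planned enrolment of at least 50. The point below does not depend on this figure.

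**Wording.** Compared character by character, question 3 under behavioural beliefs and question 3 under normative beliefs are identical.

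**What each question refers to:**

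| Block | Question 1 | Question 2 | Question 3 |
| --- | --- | --- | --- |
| Behavioural | advantages | disadvantages | anything else about the act |
| Normative | who would approve | who would disapprove | anything else about the act (same words as above) |
| Control | what enables | what hinders | other issues about the act (own wording) |

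**Against the Protocol's definitions.** Section 2.8.1 derives attitude from beliefs about a behaviour and the evaluation of its outcomes, and subjective norm from how a person perceives the beliefs of others. Normative questions 1 and 2 meet the second definition. Normative question 3 refers to the behaviour alone, so as worded it matches the first.

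**Consequence.** Of the three normative questions, two ask about norms and one does not. A respondent with a normative belief that does not fit approval or disapproval by a nameable person or group has no question inviting it. Content coding can move a misplaced answer to the right construct, but it has nothing to work on where no answer was prompted.

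**The case against.** Several points count on the other side.

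- **Context.** The question follows two questions on approval and disapproval and stands under a normative heading, so some respondents will answer it with norms in mind. This stands: loss of normative beliefs is possible, not certain.
- **The two direct questions are open as to whom they cover.** Any individual or group may be named. This also stands, and it limits the loss.
- **The control block also closes with a generic question.** True, and so a generic closing question is not by itself the fault. The difference is that the control block has its own wording, while the normative block reuses a question already put for another construct.
- **Later checks.** Section 3.2.5 provides a trial of the draft by five respondents, expert comment on construct validity and Cronbach's alpha; section 3.2.6 f repeats alpha for each construct. These can expose an attitude item sitting in the norm scale. They cannot be relied on to supply a belief that was not elicited.

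A reader might go further and infer that attitude beliefs are counted twice when the beliefs are ranked by frequency. The Protocol does not support that. Section 3.2.3 describes coding by theme. It does not say that mentions rather than respondents are counted, that the constructs are pooled, or that an answer is filed under the heading where it was written. With a separate list for each construct the attitude count would not rise at all, and if the 75% rule refers to distinct beliefs a repeat adds none.

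A reader might also count the prompts as four behavioural, two normative and three control. That treats the normative closing question by its content and the equally generic control closing question by its heading. By heading alone the count is three each.

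**Conclusion.** The duplication is plain on the page, and by the Protocol's own definition the repeated question does not ask for normative beliefs. The normative section therefore has no norm-specific open probe. It may gather attitude statements and may miss normative beliefs, which could weaken the subjective-norm items in the survey regression.

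The size cannot be estimated. It depends on how respondents read the repeated question and on how many hold normative beliefs that the two direct questions do not reach; the Protocol gives no figure for either. Any stated percentage of lost or misfiled beliefs would be an invention.

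The reach is limited. Only questionnaire development for objective 1 is affected. Nothing changes in the randomisation, sample size, power or primary outcome of the cluster trial. This is a small improvement worth making because it is so cheap.

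**What to change.** In Appendix II, replace question 3 under normative beliefs with one that refers to other people's views, for example: *Is there anything else you associate with other people's views about your measuring the patient's BP?* Leave question 3 under behavioural beliefs as it is.

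The cost is one reworded question, provided the change is made before the elicitation study starts. If the Protocol has already been approved, section 3.8 requires the ethics committee to be told of the amendment. No sample size, timeline or analysis changes.

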**Control beliefs (perceived behavioural control)**

1. What factors or circumstances enable you to measure the blood pressure of adolescents living with HIV?
2. What factors or circumstances make it difficult or impossible for you to measure the blood pressure of adolescents living with HIV?
3. Are there any other issues that come to mind when you think about measuring the blood pressure of an adolescent living with HIV?

**DATA EXTRACTION FORM**

| **Name of reviewer:……………………………………. Date:………………….** | | | |
| --- | --- | --- | --- |
| **Demographic characteristics** | | | |
| **Question No.** | **Variable** | **Variable code** | **Values** |
| 1) | Folder ID | FID | ………………….. |
| 2) | Study ID | SID | …………………. |
| 3) | District/Municipality | AREA | ………………….. |
| 4) | Facility | FAC | ………………….. |
| 5) | Date of data collection | DATE | dd-mm-yyyy………………………. |
| 6) | Sex | SEX | 0-Female  1-Male |
| 7) | Age (years) | AGE | ……………………………. |
|  |  |  |  |
| 8) | Occupation | OCC | ………………………………. |
| 9) | Highest educational level | EDUC | 1-No formal education  2-Primary school  3-High school  4-Tertiary |
| 10) | Marital status | MSTAT | 1-Single  2-Married  3-co-habitting |
| 11) | Religion | REL | 1-Christian  2-Muslim  3-Other (specify) |
| **Section II – Clinical characteristics** | | | |
| **12** | Date of HIV diagnosis | DD_HIV | dd-mm-yyyy………………………. |
| **13** | Age at HIV diagnosis | **AD_HIV** | ………………….years |
| **14** | HIV Type |  | 1-I 2-II 3-I & II |
| 15 | Weight at baseline | WT_BASE | ……………………………(Kg) |
| 16 | Weight at end line | WT_END | ……………………………(Kg) |
| 17 | Height | HT | ……… (m) |
| 18 | Date of ART initiation | DAI | dd-mm-yyyy………………………. |
| 19 | Age at ART initiation | AAI | …………………………………. |
| 20 | WHO Stage at ART initiation | WSI | 1-1  2-2  3-3  4-4 |
| 21 | Current ART regimen | CAR | ----------------- |
| 21 | Previous ART Regimen | PAR | ……………………….    ………………………. |
| 22 | Viral load at baseline | VL_B | 1-Suppressed  2-Unsuppressed  3-None |
| 23 | Viral load at baseline | VL_B | 1-Suppressed  2-Unsuppressed  3-None |
| 24 | Systolic BP at last visit | SBP | 1………..  2.Not recorded |
| 25 | Diastolic BP at last visit | DBP | 1………..  2.Not recorded |
| 26 | Action taken on BP | BP_ACT | 1. None  2. Rechecked to confirm  3. Given appointment to recheck  4. Counselled on lifestyle  5. Referred |
| 26 | Smoking | SMK | Yes___ No___ Ex____  If Yes: Type___________  Number /day or week_______ |
| 28 | Alcohol use | ALC | Yes___ No___  If Yes (Check one):  Every day___ ≥ Once weekly ___ ≥ Once monthly___ |
